### 1.5. Cognitive Markers Associated to AD Neuropathology

Episodic memory loss—as the most sensitive and specific cognitive marker—has long been considered “the gold standard” for the diagnosis of cognitive impairment due to AD, although its manifestation in healthy aging is quite common [56]. Early detection of incipient dementia pathophysiology is difficult during aging [6], and neuropsychologists have to schedule periodic follow-up assessments at clinics to confirm the progression of cognitive impairment and restrictions in personal and instrumental autonomy to consider a patient to have fulfilled the diagnostic criteria of dementia. Evidence from the literature indicates that SN deficits can indicate individuals at higher risk of developing AD early [29], with strong implications for timely intervention. SN deficits have the potential for early detection of cognitive alterations in topographical orientation since they have higher specificity in distinguishing AD from healthy aging [57,58], as well as from other dementia types [59,60,61]. Further, animal models of AD pathophysiology have reported on how navigation-specific brain areas are primarily affected, rather than episodic memory ones [62,63]. SN is one of the earliest cognitive domains to be impaired in patients with AD that may result in SD. It refers to instances where AD patients are unaware of where they are and are unable to reach their intended location [64]. It behaviorally manifests in AD patients making navigation errors when they go out of their community, which can lead to an increased risk of going missing in both familiar and unfamiliar environments [65], with negative consequences for personal safety, including potential injuries and, in the worst cases, even death [66]. Remarkably, incidents of the patient going missing restrict patient’s autonomy and self-efficacy and increase the caregiver’s burden [67]. In line with previous studies [64,68], AD patients may present with “moments of hesitation” while walking in their familiar environments. A “moment of hesitation” is defined as the participant slowing down/stopping and looking around to aid orientation or verbally admitting that he/she is unsure about their whereabouts. This is consistent with the fact that when participants exhibit hesitant walking, more variation would be seen in their step intervals, as compared to when they are more confident in wayfinding (cf., [25]). Further, when an elderly person loses their sense of direction, he/she moves to come back as soon as possible to reach the original start point and may present with some distressing symptoms and spatial anxiety [69], potentially influencing cardiac and respiratory physiological functions. Considering SN dysfunction as a cognitive biomarker of AD, interventions that may help in preventing SD using the most advanced wearable technology may contribute to detecting and treating the initial manifestation of the disease. SD has been specifically described in AD and MCI patients as deficits in route learning, free recall or recall of the temporal order of the landmarks, landmarks recognition and location on a 2D map, route drawing, and evaluating directions [70]. However, to date, no study in the literature has pointed out physiological correlates (e.g., physiological stress indexes) that might be associated with them. Deterioration in SN, manifested in poor hippocampus-dependent allocentric navigation, may also occur before the clinical onset of dementia [71]. A study investigating navigation skills as a function of the APOE allele found that patients with amnestic MCI and APOE-ε4-positive allele performed more poorly on both allocentric and egocentric tests than amnestic MCI patients with the APOE-ε4-negative allele [72]. Further, it has been demonstrated that virtual and ecological SN tasks can differentiate the SN performances of amyloid-positive MCI patients and amyloid-negative MCI patients ([16,73]). Finally, from the earliest stages of AD, the presence of specific impairment in the ability to encode and store an allocentric hippocampal representation and then to translate it into an egocentric parietal representation has been recently observed, and it has been proposed as a specific cognitive process that may be useful in supporting the recall of spatial scenarios too [74], which could be impaired even in premorbid AD.

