### 2.4. Statistical Analysis

Data distribution will be first checked on collected variables by assessing skewness and kurtosis values, by performing normality and heteroscedasticity tests, and by visually inspecting histogram and Q–Q plots. Based on data meeting or non-linear model assumption, either parametrical or non-parametrical analyses will be performed. By means of the R marco *pwr* [86], the minimal sample size has been set as 76 participant, based on a power analysis for a multiple regression model that took into account the following parameters: α = 0.05; 1-β = 0.9; *f*^2^ = 0.15 (medium effect size, in order to be conservative) [87]; and numbers of predictors: 3 (age, APOE genotypes, and belonging to each group, with the last two predictors as dummy variables).

We will detect the route disorientation scores, i.e., WTs and MsH, as already described in Puthysserypaddy et al. [64]. Accordingly, all the violations in terms of deviations from the pre-established return path (i.e., movement at an intersection onto a different path as compared to the original one, or non-roadable walkways) will be written down by the experimenter as WTs in a pre-set paper grid for *Route A*. The overlaps with the *Route A* return path, and, likewise, non-roadable walkways will be written down by the experimenter as WTs in a pre-set paper grid for Route *B*. Further, we will detect the MsH as the participant either slows down/stops and looks around to aid orientation or verbally admits to the experimenter that he/she is unsure about his/her whereabouts, both for *Route A* and the *Route B* return path.

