In addition to the experimenter visually identifying and recording the frequency of the MsH with a stopwatch and a pre-set paper grid, we will measure this variable more objectively using the Howdy Senior integrated accelerometer. For this purpose, we will use the motion sensor of the sensorial body measuring the individual’s linear acceleration in the three axes (i.e., x, y, z). To segment the magnitude signals, according to Schaat et al. [88], we will adopt time intervals of 10 s, with an overlap of 5 s between subsequent intervals because a 10 s segment is sufficiently long to capture multiple steps during walking, thus revealing important behavioral changes. In this way, we will detect the MsH as a signal flattened along the three axes. Further, given that physiological parameters may alter depending on the MsH, we will also investigate the relationship between step variability and co-occurring time-dependent cardiac and respiratory parameters detected by the Howdy App, expressed as mean values, via Pearson’s correlation coefficients or their non-parametric equivalent (i.e., Spearman’s rank order correlation). Moreover, we will run a one-way ANOVA (or its non-parametric equivalent) to compare performances of the three subgroups on gait parameters collected through the Aptive app and the SSNC questionnaire. In order to explore potential association between specific neurocognitive functions and SN impaired abilities, Pearson correlations or their non-parametric equivalent (i.e., Spearman’s rank order correlation) will be further performed between the AppleGame/DNT-mv results and the neuropsychological tests used in the sending centers, especially visual–constructive skills and executive functions (see Appendix A). Given the difference of the neuropsychological battery used in the sending centers, we will group tests according to the primary cognitive domain involved and we will divide the scores obtained in a dichotomous way for each participant according to the reported cut-off values in the test manuals, i.e., 0 = pathological performance; 1 = normal performance.

Finally, a linear/generalized linear regression analysis will be run, taking into account the drop errors of the AppleGame subtasks—considered one at a time—as independent variables, and the total number of “wrong turns” (WTs)/total number of “moments of hesitation” (MsH) (in seconds) of the DNT-mv as dependent variables.

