**Figure 6 jpm-14-00192-f006:**
[figure not shown]
Howdy Senior system components. The electronic unit (white) detects heart rate, respiratory rate, and body position. It is equipped with five automatic snaps on the back and communicates with the Howdy app via Bluetooth. The electronic unit can be combined with different textile units: male/female top with sensors and belt. The electronic unit and textile unit are connected using the automatic snaps. The Howdy Apps works on smartphones and tablets running Android 8.0 or later.

**Table 1 jpm-14-00192-t001:** Cardiac, respiratory, and accelerometer parameters collected by the Howdy Senior App.

**Cardiac system functions** *Time domain over RR intervals parameters*	avgRR: mean of R2R interval; SDRR: standard deviation of R2R interval; avgHR: mean of Heart rate; SDHR: standard deviation of Heart rate; MSSD: mean of square successive differences between normal heartbeat; RMSSD: root mean square of square of successive differences between normal heartbeat; lnRMSSD: natural log of RMSSD; hrvScore: normalized lnRMSSD value using as scaling factor the value 6.5; RR50: number of successive absolute difference greater than 50 ms; pRR50: percentage of number of successive absolute difference greater than 50 ms over the number of elements in the analyzed window; SD1: standard deviation along the minor axes of the Poincare plot; SD2: standard deviation along the major axes of the Poincarè plot; Stress index.
**Cardiac system functions** *Frequencies domain over RR intervals parameters*	LF: power in the low frequency band affected by sympathetic nervous system (SNS); HF: power in the high frequency band affected by parasympathetic nervous system (PNS); LF/HF: ratio between the power in low and high frequency band.
**Respiratory system functions**	avgBR: mean of BR; SDBR: standard deviation of BR.
**Accelerometer parameters**	AccXavg, AccYavg, AccZavg: mean of accelerations for X, Y, Z axes; AccXsd, AccYsd AccZsd: standard deviation of accelerations for X, Y, Z axes; AccXrms, AccYrms, AccZrms: root mean square of accelerations for X, Y, Z axes.

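### The physiology hypothesis concerns moments of hesitation, but the planned correlation uses step variability, a proxy whose sign and meaning are not fixed

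*Protocol article*

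**What the plan says.** All references are to the protocol article.

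- **Hypothesis.** The Discussion (section 3) anticipates that changes in physiological parameters, especially respiratory ones, go with MsH. Section 2.4 motivates the analysis in the same way: "given that physiological parameters may alter depending on the MsH".
- **Planned analysis.** The same sentence of section 2.4 continues: "we will also investigate the relationship between step variability and co-occurring time-dependent cardiac and respiratory parameters detected by the Howdy App". The physiological values are to be means, and the coefficient Pearson or Spearman.
- **Observer definition of MsH.** Section 2.4 counts an MsH when "the participant either slows down/stops and looks around to aid orientation or verbally admits" to being unsure of the location. The observer uses a stopwatch and a paper grid.
- **Accelerometer definition of MsH.** Section 2.4: "we will adopt time intervals of 10 s, with an overlap of 5 s between subsequent intervals"; then "In this way, we will detect the MsH as a signal flattened along the three axes".
- **Premise about gait.** Section 1.5 says that "when participants exhibit hesitant walking, more variation would be seen in their step intervals" than in confident wayfinding.
- **Candidate measures of variability.** Table 1 lists the "standard deviation of accelerations for X, Y, Z axes". The text after Table 1, on the Aptive app, links step variability to a speed estimated from the accelerometer.

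**The concern.** The hypothesis and the analysis name different variables. This is a stated choice rather than a detail left out: the sentence just before the planned correlation sets up an accelerometer detector of MsH, and the next sentence uses a stand-in.

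A stand-in is acceptable if it moves in one direction with the thing it replaces. Here the article gives two signatures of hesitation. One implies that variability goes up (irregular steps), the other that movement fades (flat signal). If both occur in the same walks, a single correlation coefficient mixes them.

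At stake is the reading of a result that section 1.5 presents as new, since it says no study has yet reported physiological correlates of spatial disorientation. A null or negative coefficient could be taken as absence of a physiological response when there is one. A positive coefficient could not be attributed to MsH.

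**Working it through.** The article gives no figure for this analysis, so there is nothing to reproduce. The check has two steps. Apart from the 10 s window and 5 s overlap, all inputs are assumptions and not trial data.

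**Step 1: is step-interval SD monotone in hesitation within a 10 s window?** Assume a confident step interval of 0.55 s (SD 0.025 s) and a slowed one of 0.9 s (SD 0.2 s).

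- Confident walking: SD = 0.025 s.
- Slowed, irregular walking throughout: SD = 0.2 s.
- A 3 s stop inside the window: about 12 intervals of 0.55 s and one of 3 s (12 × 0.55 + 3 = 9.6 s). SD ≈ √(1/13 × 12/13) × (3 − 0.55) = 0.266 × 2.45 ≈ 0.65 s.
- Standing still for the full 10 s: no intervals, so no SD.

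The value rises with slowing, rises further with a short stop, and cannot be computed in a complete stop. It is not monotone in the share of the window spent hesitating.

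**Step 2: what happens to the correlation?** The simulation used 400 walks per scenario, each of 150 s with 0 to 4 hesitations, and 10 s windows overlapping by 5 s. Breathing rate per window = 18 + 4 × (hesitating share of window) + normal error with SD 1, so the true association is positive throughout. Step-interval SD was called undefined when a window held fewer than three intervals. Entries are Spearman coefficients with breathing rate; the last row uses each participant's mean breathing rate.

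| Measure | Stops 2–5 s | Stops 5–10 s | Stops 12–25 s | Slowing 3–10 s |
|---|---|---|---|---|
| Windows with undefined step-interval SD | 0% | 1.4% | 16.6% | 0% |
| Step-interval SD, window, undefined dropped | +0.15 | +0.03 | −0.08 | +0.36 |
| Step-interval SD, window, undefined set to 0 | +0.15 | −0.01 | −0.45 | +0.36 |
| Acceleration SD, window | −0.22 | −0.37 | −0.63 | −0.38 |
| Step-interval SD, whole route, per participant | +0.56 | +0.83 | +0.92 | +0.78 |

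Where a window was hesitation throughout because the person stood still, step-interval SD was undefined in 100% of cases. At route level, step-interval SD tracked total seconds of hesitation closely (0.95 to 0.96), because each stop adds one very long interval.

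A separate check took the SD of speed as the measure, with breathing raised by 3/min times the hesitating share (SD 2). Window-level coefficients were +0.10 (2–5 s stops), +0.20 (5–10 s), −0.06 (12–25 s) and +0.16 (slowing). Per participant they were +0.20 to +0.81.

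The same true response thus gives a positive, near-zero or negative coefficient, according to the measure, the unit of analysis and the form and length of the hesitation.

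**The case against.** A reader might infer more: that an MsH contains no steps, so that step variability is always undefined or at its minimum there and the correlation is bound to be null or reversed. The documents do not support this, for four reasons.

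- MsH includes slowing and verbal admission, during which steps can continue, and no threshold is given for a flattened signal.
- Stops shorter than 10 s leave steps in the window and can raise variability.
- The text after Table 1 ties step variability to speed. Speed is defined at a stop (zero), and its SD kept the expected sign in three of four window-level scenarios.
- The physiological values are to be means, so a participant-level analysis is a possible reading. At that level step-interval SD keeps its sign and follows hesitation well. Against this, the wording about co-occurring, time-dependent parameters points to an analysis within the walk.

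Two further objections carry weight. A negative coefficient with acceleration SD is not a lost association: it is what one expects if hesitation flattens the signal, although it runs opposite to the premise in section 1.5. And the formula, the unit of analysis and the handling of windows without steps are details that an article may leave to the full protocol or analysis plan, so their absence is not held against it.

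None of this removes the mismatch between the hypothesis and the variable analysed, which is explicit in the text. Sections 1.5 and 2.4 can be reconciled as two forms of hesitation, slowed walking and stopping, but that is why one window-level measure of variability cannot stand for both.

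**Conclusion.** The point holds in this form: the hypothesis is about MsH, the analysis uses step variability, and at the 10 s window level step variability is not a monotone measure of MsH. A real physiological response at MsH can therefore appear as positive, null or negative, and the coefficient should not be read as the MsH-physiology association.

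Failure is possible but not certain. In the main simulation the window-level coefficients ran from +0.36 to −0.63, and the route-level ones from +0.56 to +0.92. These figures show direction only. They rest on assumed gait, stop lengths and breathing response, and they do not predict the trial's result.

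The matter is moderate in weight. It affects one stated hypothesis, but neither the sample size calculation nor the regression for the second endpoint. It is best treated as a cheap improvement.

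**What to change.** Make MsH the exposure. Classify each segment as MsH or non-MsH from the observer record and the accelerometer detector, and compare the co-occurring cardiac and respiratory values between the two within participant. Where possible, separate stops from slowed walking, since the two have different accelerometer signatures.

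Keep step variability as a secondary measure of hesitant walking, limited to segments that contain steps, and do not interpret it as the MsH-physiology association.

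The cost is one extra classification step on data already planned for collection. The main limitation is that the MsH versus walking contrast partly reflects lower physical exertion at stops. The current correlation shares this limitation; it should be acknowledged when the result is interpreted, and separating stops from slowing helps to show how much it matters.

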Before the navigation of the urban garden, all participants will equip the Howdy Senior^©^ (Comftech S.r.l., Monza, Italy) device (Figure 6), a wearable monitoring system. All participants will be recorded according to cardiac and respiratory parameters *at rest* for five minutes and during the naturalistic experiment (Table 1). These data will be available thanks to the instant reports produced by the connected “Howdy Senior App” set up on the experimenter’s smartphone.

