## 3. Discussion

In relation to the first endpoint, we expect that patients with MCI due to AD will show significantly more SN deficits than healthy controls and individuals with SCD, both in the AppleGame and in the DNT-mv, in terms of higher drop errors on BPI, LPI, and PPI and higher amounts of WTs and MsH, respectively. Virtual and ecological deficits may reflect a cognitive inefficiency of the entorhinal cortex, where AD neuropathology manifests early [25]. It has also been demonstrated that virtual and ecological SN tasks can detect the SN alteration of amyloid-positive MCI patients [89,90]. According to Colmant et al. [91], we also presume that APOE-ε4 carriers will report a PPI deficit in the VR task differently from non-carriers, regardless of subgroup.

Furthermore, we also anticipate that significant physiological parameters modifications (particularly, respiratory function) may be particularly associated with MsH, given that anxiety rather than depression significantly influences SN abilities in non-demented elders [92]. Starting from difficulties in spatial orientation evaluated in naturalistic experiments able to modify gait [93], we finally assume that patients with MCI due to AD will perform worse than SCD and healthy controls in terms of “Time” and “Speed”, and report significant differences in “Direction”, all variables collected by the Howdy Aptive app in the open-space naturalistic task.

In relation to the second endpoint of the research, we assume that the drop errors obtained in the VR task may predict the route disorientation scores of the naturalistic task. In particular, we expect a causal relationship between the BPI drop error of the AppleGame and the *Route A* return path of the DNT-mv, as well as between the LPI drop error of the AppleGame and the *Route B* return path of the DNT-mv, because they mainly rely on egocentric and on allocentric navigation, respectively. A recent systematic review and meta-analysis [44,94] has outlined that the association of navigational tasks performed in virtual and real environments needs to be deeply clarified. In light of this, we believe that the AppleGame could represent a validated technique with which to detect, in laboratory, early SN deficits in populations at risk of dementia conversion to provide high-quality, time-limited diagnosis. It is a cost-effective tool able to predict real-life SN impairment that should be routinely used in clinical practice.

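### The correlation meant to link physiology to hesitation leaves the unit of its means unstated, does not separate within-person from between-person association, and makes no stated use of the rest recording

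*Protocol article*

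**What the plan says.** Section 3 (Discussion) of the protocol article states the expectation that "significant physiological parameters modifications (particularly, respiratory function) may be particularly associated with MsH", where MsH are moments of hesitation. Section 2.4 motivates the analysis in the same way, by physiology possibly altering with MsH.

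The planned test, also in section 2.4, is stated as follows: "we will also investigate the relationship between step variability and co-occurring time-dependent cardiac and respiratory parameters detected by the Howdy App, expressed as mean values", examined "via Pearson’s correlation coefficients or their non-parametric equivalent (i.e., Spearman’s rank order correlation"). No participant term, repeated-measures structure or change score is named.

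Just before this, section 2.4 cuts the acceleration signal into windows: "we will adopt time intervals of 10 s, with an overlap of 5 s between subsequent intervals". MsH are to be read from it as a flattened signal on all three axes, alongside the experimenter's own record.

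Section 2.3.2 describes the physiological recording: "All participants will be recorded according to cardiac and respiratory parameters", first for five minutes at rest and then during the outdoor task. Table 1 lists the parameters the app delivers, including "hrvScore: normalized lnRMSSD value using as scaling factor the value 6.5".

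**The concern.** The hypothesis is about change within a person: breathing or heart rate differs while someone hesitates from what it is while the same person walks on. A simple correlation does not isolate that contrast. What it estimates depends on what one data point is, and the text leaves this open.

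- **One mean per participant.** The coefficient says whether people with more variable steps also have, say, faster breathing. Age, fitness and diagnostic group can produce or hide such an association without any response to hesitation.
- **One mean per window, all windows pooled.** The coefficient mixes within-person and between-person association, and its p-value counts each window as a new participant.

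The rest recording is the natural control for stable differences between people, yet section 2.4 uses it nowhere. Hesitation is also not the variable being correlated. Step variability stands in for it, although MsH will be available directly.

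At stake is one stated expectation of the study. A null result could simply reflect dilution, and a positive one could reflect differences between people or false precision.

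**Working it through.** The document states no figure for this analysis, so there is none to reproduce. The check follows each reading through with assumed values.

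**Inputs from the protocol.** 76 participants; 10 s windows overlapping by 5 s; five minutes of rest; Route A of 80.5 m; the Table 1 parameter list.

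**Assumed, because the documents give no values.** Between-person SD of the physiological measure 1.5 to 3 units; within-person SD 1.5; 40 independent windows per person; share of windows with hesitation averaging about 17% (Beta(2,10)); true rise during hesitation 0 to 2 units; step variability equal to the hesitation indicator plus noise of SD 0.5. Each simulated scenario used 1,000 runs.

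**Reading 1: one mean per participant** (between-person SD 3, rise 1 unit)

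1. Variance of the true share: 2×10/(12²×13) = 0.0107. Variance of a person's observed share: 0.0107 + (1/6 − 1/36 − 0.0107)/40 = 0.0139.
2. SD of mean step variability: √(0.0139 + 0.25/40) = 0.142.
3. SD of the mean physiological value: √(9 + 2.25/40 + 0.0139) = 3.01.
4. Expected correlation: 0.0139/(0.142 × 3.01) = 0.03. With 76 people, 80% power needs a correlation of about 0.32.
5. After subtracting a rest mean (error variance 2.25/30), the SD in step 3 becomes √(2.25/40 + 2.25/30 + 0.0139) = 0.381. The expected correlation becomes 0.0139/(0.142 × 0.381) = 0.26.

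Simulated probability of p < 0.05:

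| True rise | Participant means | Means minus rest | Within-person |
|---|---|---|---|
| 0.5 | 0.05 | 0.21 | 0.97 |
| 1 | 0.07 | 0.63 | 1.00 |
| 2 | 0.08 | 0.99 | 1.00 |

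The rest-adjusted column is optimistic. It assumes that walking itself shifts everyone equally from rest.

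**Reading 2: pooled windows, no true association**

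With K windows per person, the variance of the correlation is inflated by about D = 1 + (K − 1) × ICC(x) × ICC(y), where each ICC is the between-person share of variance. The false-positive rate is then about 2 × [1 − Φ(1.96/√D)].

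- Between-person SDs 1.5 (physiology) and 0.15 (step variability): ICCs 0.50 and 0.083; D = 1 + 39 × 0.50 × 0.083 = 2.6; rate about 0.22 (simulated 0.21).
- SDs 3 and 0.3: ICCs 0.80 and 0.265; D = 9.3; rate about 0.52 (simulated 0.54).
- SDs 3 and 0.5: ICCs 0.80 and 0.50; D = 16.6; rate about 0.63 (simulated 0.66).

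Where people differ in step variability only through their share of hesitation, the simulated rate was 0.13. The within-person analysis stayed at 0.04 to 0.05 throughout. These simulations used independent windows, so the extra dependence from overlap is not included.

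The number of windows is also an assumption. One traverse of Route A gives (80.5 − 10)/5 + 1 ≈ 15 windows at an assumed 1 m/s (76 × 15 = 1,140 points) and (161 − 10)/5 + 1 ≈ 31 at 0.5 m/s (76 × 31 = 2,356 points). With K = 15 the three formula rates fall to 0.12, 0.33 and 0.45, still well above 0.05.

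**Parameter list.** Table 1 holds 13 time-domain, 3 frequency-domain and 2 respiratory parameters, 18 in all. By definition RMSSD is the square root of MSSD, lnRMSSD its logarithm and hrvScore a rescaling of that; SD1 is in effect proportional to RMSSD. On one recording segment these five give the same Spearman coefficient. Under Pearson, which is named first, they overlap strongly but are not identical.

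**The case against.** **Timing is not discarded.** A reader might infer that the plan ignores within-person timing and so cannot show any link with hesitation. The text does not support that. The planned sentence itself speaks of co-occurring, time-dependent parameters, and the windows are defined just before it. With per-window means an association could appear, though with invalid p-values. The fair criticism is an unstated unit together with a method that is unsuitable under either reading.

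**A condensed article may leave the baseline to a fuller plan.** This stands in part: silence does not mean the rest data will go unused. But the article does fix the variables, the summary and the test, and a fuller plan would have to replace that choice, not merely add detail.

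**Multiplicity.** A reader might infer 18 tests and a false-positive chance of 1 − 0.95^18 = 0.60. The plan never says that every Table 1 parameter will be tested, and the figure needs independence, which the duplicates contradict. Counting the five as one gives 1 − 0.95^14 = 0.51, again an upper bound. If only the three averages (avgRR, avgHR, avgBR) are meant, it is 1 − 0.95^3 = 0.14. The point does not rest on any of these.

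**Export is not established.** The windows are assigned to the acceleration signal only, and section 2.3.2 mentions app reports. Nothing shows that physiology can be exported per 10 s window. This stands, and the fix allows for it.

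**Limited stakes.** Section 2.4 introduces the analysis as an additional one, and the sample size is not tied to it. This also stands.

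**Conclusion.** The point holds in this form: the plan states a within-person expectation, tests it with a simple correlation whose unit is unspecified, and gives the collected rest recording no stated role. Per-participant means give a valid but between-person test, with very little power for the change of interest; pooled windows give p-values that are too small.

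The sizes reported (power 0.05 to 0.08 against 0.97 to 1.00; false-positive rates 0.13 to 0.66 in simulation) depend on the assumed variances, hesitation share and window count, and are illustrations. The direction needs only that people differ stably in heart rate and breathing and, for pooling, in step variability too. The documents do not support saying that the analysis can show nothing, or that a 60% error rate is built in. This should be corrected, but it does not touch the main group comparisons or the prediction of real-world performance.

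**What to change.** 1. State in section 2.4 whether each mean is per participant or per window.
2. Express each parameter as change from the participant's own rest value, or adjust for that value.
3. If time-resolved physiological data can be exported, compare MsH with non-MsH windows within person, using a mixed model with a random participant intercept and allowance for autocorrelation between overlapping windows. Do not adjust for walking speed: slowing or stopping is part of the definition of MsH, so the adjustment would remove much of the exposure.
4. If only per-participant values are available, correlate change from rest with each participant's MsH and describe the result as a between-person association.
5. Name mean breathing rate (avgBR) as the main parameter, in line with the Discussion's emphasis on respiration. Keep one of MSSD, RMSSD, lnRMSSD, hrvScore and SD1, and label the other parameters exploratory.

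The cost is moderate extra analysis work and fewer parameters reported as tests. Steps 2 and 4 use recordings already planned; step 3 depends on what the device can export, which should be confirmed first.
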